### Sample size

Sample size calculations were based on a recently published study by Bauersfeld et al. assessing short-term fasting during chemotherapy of breast and ovarian cancer patients (13). A sample size of 48 patients per group is necessary to detect a mean difference of 9.1 points on the FACIT-FS^©^ scale with a standard deviation of 13.7 points and a power of 90% and α=0.05 with a two-sided independent t-test. To account for possible drop-outs, a sample size of 55 per group at baseline is planned.

### Data monitoring, interim analysis and trial termination

Data will be collected on a personalized case report form at the predefined time points depicted in **Table 1**. Data will be entered in a protected database (RedCap). Only authorized members of the IFAST study team will be allowed to enter, store and access participant data. Paper-based data will be stored at the department of obstetrics and women’s health at the University Medical Center Mainz. Clinical routine data assessments will be stored in the respective patient’s clinical files at the University Medical Center Mainz and St. Josef’s Hospital.

The safety of IF has been proven in many smaller studies, including our pilot trial (9) for healthy people as well as patients under chemotherapy (25). No severe adverse events were observed; thus, no interim analysis is planned. The trial can be terminated by the patient at any time without the risk of negative consequences by withdrawing consent. The discontinuation of the intervention can be decided upon by the investigator due to medical reasons, including the reduction of the BMI to <18 kg/m^2^, acute severe CHT induced side-effects requiring hospitalization or acute, severe non-chemotherapy related medical illnesses requiring hospitalization. Patients terminating the intervention will be asked to fill out the questionnaires outside of the study protocol.

A data monitoring committee consisting of a medical doctor and a study nurse will be overseeing the study visit schedules. All investigators will be obliged to report any changes or deviations of the protocol to the data monitoring committee. Any serious adverse events will be reported to the data monitoring committee and discussed with the principal investigator within 48 hours of occurrence. The termination of the trial for the participant can be decided upon based on the criteria mentioned above by the principal investigator. The termination of the whole trial can be determined by the principal investigator together with the data monitoring committee due to unexpected serious adverse events based on the intervention or due to failure to recruit the planned number of patients.

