### Outcome measures

#### Primary outcome

Primary outcome of this study is the difference of the mean change in fatigue from baseline to last follow-up time point of the active trial period (3 months) between the IF group and the control group. A variation of up to ± 1 week for trial termination is allowed due to potential delays of CHT (e.g. due to insufficient blood values or public holidays).

Fatigue is measured after each chemotherapy treatment using the Functional Assessment of Chronic Illness Therapy-Fatigue Scale (FACIT- FS©). This questionnaire assesses cancer therapy related fatigue. It is part of the FACIT-F© questionnaire (22) which is a combination of the Functional Assessment of Cancer Therapy general core questionnaire (FACT-G©) and the FACIT-FS©. The FACIT-FS© includes 13 fatigue related questions, which are rated on a 5-point Likert scale (not at all to very much) over the last 7 days. Scores will be calculated according to published scoring algorithms.

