### Statistical analysis

Patients will be randomized to the intervention or control group (1:1) stratified by tumor entity and study site. The primary endpoint, the difference of the mean change of fatigue over a period of three months as measured by the FACIT-FS© score, will be compared between both groups using mixed models. Confounders such as age, type of CHT, neoadjuvant/adjuvant vs metastatic treatment, the Eastern Cooperative Oncology Group performance status (ECOG), histological tumor grade, and Fédération Internationale de gynécologie et d’Obstetrique (FIGO) -stage will be included in the mixed models. Laboratory data, as well as QoL questionnaire-based outcomes will also be assessed using mixed models. Missing data for the primary outcome as well as secondary outcomes with the potential to become main outcomes in subsequent larger trials will be imputed. Where possible, missing questions from FACT^©^ questionnaires will be prorated using the average of the other answers in the subscale (prorated subscale score = [sum of the item scores]*[N of items in subscale]/[N of items answered]) as long as more than 50% of the items are answered. Data will be imputed by drawing values from the distribution of the control group (jump to reference).

A comprehensive summary will be given for primary and secondary endpoints, including absolute and relative frequencies for categorical and binary variables as well as mean and standard deviation or median and interquartile range and minimum-maximum for all data with at least interval scale level. Pathological response rates after neoadjuvant CHT will be compared using the Chi square test. Radiological response rates (complete response, partial response, stable disease, and progressive disease) will be compared between the arms at 3 months and 6 months using the Mann-Whitney-U-tests. The occurrence of any adverse event as well as the occurrence of grade 3 or higher adverse events will be compared between both groups using the Chi square test. And a list of immunological and metabolic parameters will be compared between both groups using the Mann-Whitney-U test. A paired Wilcoxon test will be used to compare the change in BMI over three months between both groups.

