Analyses will be performed as (1) modified intention-to-treat (ITT) population including all patients randomized who have at least received the first chemotherapy cycle. Patients will be analyzed in the group they were randomized to; (2) per-protocol (PP) sets, including all patients who have at least completed one/two/three or all chemotherapy cycles without major protocol violations. Safety will only be assessed in the per-protocol subset. Subgroup analyses will be performed by tumor type and type of CHT regime for groups with an adequately high number of participants. Furthermore, the parameters will be displayed graphically, and appropriate descriptive statistics will be employed. The significance level will be bilaterally set at 5%. 95% confidence intervals will be reported where appropriate. Due to the exploratory nature of secondary outcomes, no adjustments will be made for multiple testing.

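### Fatigue scores collected after a patient stops fasting may be treated as missing and replaced by control-like values, because the plan does not say whether they enter the modified ITT analysis

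*Protocol article*

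**What the plan says.** Four statements in the protocol article bear on this point.

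- **Data monitoring, interim analysis and trial termination:** "Patients terminating the intervention will be asked to fill out the questionnaires outside of the study protocol". The same section lists medical grounds on which the investigator may stop the intervention, among them "acute severe CHT induced side-effects requiring hospitalization". It then lets those same criteria decide whether the patient's trial participation ends.
- **Statistical analysis, missing data:** imputation applies to "Missing data for the primary outcome as well as secondary outcomes" that might become main outcomes of later trials. The rule is "Data will be imputed by drawing values from the distribution of the control group (jump to reference"). It does not distinguish by arm, by reason, or by whether the patient is still following her assigned diet.
- **Statistical analysis, populations:** the modified ITT set is described as "including all patients randomized who have at least received the first chemotherapy cycle", and "Patients will be analyzed in the group they were randomized to".
- **Primary outcome:** the endpoint is the change in fatigue "from baseline to last follow-up time point of the active trial period (3 months").

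No section says whether a questionnaire completed after stopping the intervention is used in the modified ITT analysis.

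**The concern.** A modified ITT analysis of the 3-month change needs the 3-month score of every included patient, on or off the diet. The trial asks stoppers for that score but labels the request as off-protocol. An analyst following this wording could reasonably leave those forms out of the primary dataset. The 3-month value would then be missing, and the single stated rule would draw it from the control arm. A real observation would have been replaced by an assumption.

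The listed medical grounds (low BMI, severe chemotherapy side-effects or other severe illness needing hospital care) make it uncertain that stoppers resemble the average control patient. If they are more fatigued, control-like values flatter fasting. If they keep some benefit, the benefit is understated.

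The undivided rule has a second effect. Taken literally, it also covers a patient who is still fasting and misses one form. Drawing her value from the control arm pulls the estimate toward no effect if fasting works. The section on study design and setting has fatigue assessed weekly over the 12 weeks, so her neighbouring scores would normally be available to the planned mixed model.

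**Working it through.** **1. The design figure.** Under Sample size the plan states: "A sample size of 48 patients per group is necessary to detect a mean difference of 9.1 points", with SD 13.7, 90% power and two-sided α = 0.05.

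n per group = 2 × [13.7 × (1.960 + 1.282) / 9.1]² = 47.6, so 48.

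The stated figure reproduces. An exact t calculation gives 48.6, so 49, with 89.6% power at 48. The design figure is not in dispute; 9.1 serves below as the yardstick.

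**2. Set-up.** Differences are signed so that positive favours fasting.

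- d = share of the fasting arm that stops the intervention (not in the document; assumed 10–30%)
- D = stoppers' true mean difference from control at 3 months (not in the document; assumed −9.1 to +9.1)
- 9.1 = effect in those who continue (assumed equal to the design effect)

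The planned 55 per group implies an allowance of 1 − 48/55 = 12.7%. That allowance is for drop-outs in each arm, not for patients who stop fasting and keep answering. It appears below only as one value in the range.

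**3. Formulas.**

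- Effect using stoppers' own scores = (1 − d) × 9.1 + d × D
- Effect if stoppers receive control-mean values = (1 − d) × 9.1 + d × 0
- Shift (imputed minus own scores) = −d × D

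**4. Results (points).**

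| d | Imputed | Own scores, D = −9.1 | Shift | Own scores, D = 0 | Shift | Own scores, D = +9.1 | Shift |
|---|---|---|---|---|---|---|---|
| 10% | 8.19 | 7.28 | +0.91 | 8.19 | 0 | 9.10 | −0.91 |
| 12.7% | 7.94 | 6.79 | +1.16 | 7.94 | 0 | 9.10 | −1.16 |
| 20% | 7.28 | 5.46 | +1.82 | 7.28 | 0 | 9.10 | −1.82 |
| 30% | 6.37 | 3.64 | +2.73 | 6.37 | 0 | 9.10 | −2.73 |

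A smaller gap shrinks the shift in proportion: at d = 20% and D = −4.55 it is 0.20 × 4.55 = +0.91.

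**5. Effect on power.** With 55 per group, SD 13.7 and the normal approximation, at d = 20% and D = −9.1 the power is about 55% with stoppers' own scores (effect 5.46) and about 80% with imputed values (effect 7.28). At d = 20% and D = +9.1 it is about 94% with own scores (effect 9.10) and about 80% imputed.

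**6. Skipped forms in patients still fasting.** If such patients truly have the full 9.1-point benefit, imputing the control mean is the D = +9.1 case. A 10% share of such gaps would cost 0.10 × 9.1 = 0.91 points.

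**The case against.** The strongest reply is that the sections can be read without conflict. A completed questionnaire is not missing, so an imputation rule for missing data does not touch it. The off-protocol wording may mean only that the patient has left the assigned regimen. Asking stoppers to keep answering is what an ITT analysis requires. This reading is available, and no section says that collected scores are discarded or overwritten. A reader might infer that real outcomes are certainly replaced, but the document does not support that. What remains is that the wording invites exclusion and nothing in the article rules it out. The same section also blurs stopping the diet with ending participation.

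Second, jump to reference is a recognised method for data truly missing after stopping treatment, and it is often conservative. As usually implemented it conditions on the patient's earlier scores, so a stopper who was already doing badly would not simply receive the control mean. The article does not state the implementation. This stands: the method is not an error in itself, and the formula above is an approximation.

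Third, a reader might infer that the rule hides harm from fasting. That is not established. Control patients also receive chemotherapy and can be hospitalised for its effects. The Introduction reports dislike of diet components as the main reason for discontinuation in an earlier fasting-mimicking-diet trial, and for such stoppers a control-like outcome is plausible. The direction is therefore open.

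Fourth, modelling detail can be left to an analysis plan that is not shown. That covers the finer points, but not a stated off-protocol label combined with a stated rule that makes no distinctions.

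**Conclusion.** The concern holds in a limited form. The article leaves open whether fatigue scores collected after stopping the intervention enter the modified ITT primary analysis. Its wording suggests that they may not, and its imputation rule would then give those patients control-like values.

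Under the assumed ranges the shift lies between about +2.7 and −2.7 points, up to 30% of the 9.1-point design effect in either direction, and it is zero if stoppers resemble controls. These figures rest on assumed shares and differences, on a 9.1-point effect in patients who continue, and on imputed values that centre on the control mean. For patients still fasting who miss a form, the rule biases toward no effect if fasting works.

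This should be corrected. It does not show that the trial's result will be biased in favour of fasting.

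**What to change.** Reconcile the section on data monitoring and termination with the two Statistical analysis passages:

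1. State that questionnaires after stopping the intervention are collected within the protocol, on the Table 1 schedule, and used as observed in the modified ITT primary analysis.
2. Separate, for data purposes, stopping the intervention from withdrawing from follow-up, so that the first does not by itself make later scores missing.
3. Restrict jump to reference to scores actually missing after stopping.
4. Handle intermittent gaps in patients still on their assigned diet as missing at random, through the planned mixed model.
5. Report a missing-at-random analysis alongside as a sensitivity analysis.

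Patients are already asked for the questionnaires, so the cost is revised wording in a few paragraphs and a little extra analysis.

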## Ethics statement

The study was registered at the German Register of Clinical Trials (DRKS) on the 8th of March, 2023 (ID: DRKS00031429). The trial will be conducted in accordance with the “Ethical principles for medical research involving human subjects” of the current version of the Declaration of Helsinki. All data will be recorded and analyzed pseudonymized and treated confidentially, by authorized study personal only. Ethics approval was obtained from the Ethics Committee of the state medical association of Rheinland-Pfalz, Germany (2020-15136_5) and the state medical association of Hessen, Germany (2023-3321-zvBO) based on protocol version 4.0 (08.01.2023). Written informed consent will be obtained from all participants and participants are free to leave at any time without giving reasons for their decision. If at any time the physical and mental health becomes jeopardized due to partaking in the study, the participation will be terminated immediately (see trial termination). Patients will be allowed to refuse additional blood draws to assess the change in PBMCs, without exclusion from the trial.

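### The same medical criteria appear to govern stopping the diet and ending trial participation, so patients selected for harm can leave follow-up and may be excluded from the per-protocol-only safety comparison

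*Protocol article*

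**What the plan says.** Under *Data monitoring, interim analysis and trial termination*, the protocol article first deals with the diet: "The discontinuation of the intervention can be decided upon by the investigator due to medical reasons". The reasons named are a fall in BMI below 18 kg/m², severe chemotherapy side-effects needing hospitalisation, and severe unrelated illness needing hospitalisation. For patients who stop, it adds: "Patients terminating the intervention will be asked to fill out the questionnaires outside of the study protocol". In the next paragraph, after the reporting of serious adverse events, it turns to the patient's place in the trial: "The termination of the trial for the participant can be decided upon based on the criteria mentioned above by the principal investigator". No separate list follows. Withdrawal of consent and termination of the whole trial are handled in sentences of their own.

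The *Ethics statement* says that if health is endangered by taking part, "the participation will be terminated immediately (see trial termination", which points back to the same section.

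Under *Statistical analysis*, the modified intention-to-treat set is every randomised patient who received the first chemotherapy cycle. The per-protocol sets are described as "including all patients who have at least completed one/two/three or all chemotherapy cycles without major protocol violations". On safety the rule is: "Safety will only be assessed in the per-protocol subset".

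**The concern.** Stopping the diet and leaving the trial are different events. A patient taken off fasting for weight loss can still be weighed, graded for toxicity and have blood drawn. When both actions hang on the same criteria, two patients with the same event can be handled differently: one stays in follow-up off the diet, the other leaves. The trial is open-label, so whoever decides knows the arm.

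The patients concerned are not a random sample, because they meet the criteria by losing weight or being hospitalised. What may be missing is the course after the harm: recovery, worsening or further events. The article uses BMI change and laboratory values to assess the safety of fasting during chemotherapy, and it records incidence and severity of adverse events. No interim analysis is planned, so the final comparison carries the between-arm safety evidence.

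The second step adds to the first. Even when later data exist, the safety comparison uses only per-protocol sets, and the article does not say where a patient taken off the diet for harm belongs.

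**Working it through.** **1. Which criteria does the back-reference mean?** Above that sentence there are three candidates: withdrawal of consent, the medical reasons for stopping the diet, and the serious adverse events in the sentence just before. Withdrawal is the patient's act, not the principal investigator's. Serious adverse events are given as something to report and discuss, not as a criterion. The medical reasons are the only list that an investigator applies to a single patient, so this is the most natural reading. Under the serious-adverse-event reading the trigger is still harm and the consequence is still the end of participation.

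**2. What is promised after a stop?** Questionnaires, placed outside the study protocol. Nothing says that CTCAE grading, weight or laboratory values continue, and nothing says that they cease.

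**3. How many patients could be involved?** The plan's own figure comes first. With a difference of 9.1, SD 13.7, two-sided 5% and 90% power, the normal approximation gives n = 2 × (1.960 + 1.282)² × (13.7/9.1)² = 47.6, so 48 per group, as stated. On drop-out: "To account for possible drop-outs, a sample size of 55 per group at baseline is planned". The allowance is 55 − 48 = 7 per arm, 7/55 = 12.7%, or 14 of 110 in all. Causes are not given, so within that allowance 0 to 7 per arm could be harm-triggered.

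**4. What follow-up is exposed?** Take three-week cycles and a stop at the week-5 visit (day 15 of cycle 2).
- Main visits: weeks 0, 3, 6 and 9 (day 1 of four cycles), week 12 and six months, 6 in all. Four remain: weeks 6, 9, 12 and six months. Weeks 6 and 9 are routine care.
- Laboratory time points: days 1, 8 and 15 of four cycles (12), week 12 and six months, 14 in all. Six have passed and 8 remain, of which 6 are routine care.

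Most later blood values should therefore exist in clinical files. The week-12 and six-month assessments are less certain, and the six-month visit is an additional study visit.

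**5. BMI illustration.** Let a share p of an arm leave, and let their mean BMI change differ by d from that of patients who stay (mean m). With everyone followed the arm mean is m + p·d; without them it is m. The between-arm error is p_IF·d_IF − p_C·d_C. Assume d = 1 point in both arms:
- equal shares lost: 0
- 7/55 lost in the fasting arm, none in control: 0.127
- none in the fasting arm, 7/55 in control: −0.127

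This scales with d: at d = 2 the extremes are ±0.25. It is an illustration, not a bound. The BMI trigger is not remote for a patient entering at the minimum of 19: a loss of just over 1 point, 1/19 = 5.3%, meets it.

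**6. Exclusion illustration.** This concerns the per-protocol safety rule, not lost follow-up. Assume a true grade 3 or higher rate of 30% in both arms (16.5 of 55), and that 7 patients in one arm are stopped, all with an event and all excluded. That arm shows (16.5 − 7)/(55 − 7) = 9.5/48 = 19.8%, a false difference of 10.2 points in its favour. If both arms lose 7 in this way, the difference is 0. This is an extreme under stated assumptions, not a forecast.

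**The case against.** A reader might infer that the protocol stops collecting safety data once the diet stops. The document does not say so. Data are to be collected at the Table 1 time points, Table 1 has no cut-off at discontinuation, and laboratory measures are to be analysed over the whole study period. The article also condenses a fuller protocol that is not shown. For a diet-only stop, the gap is inferred from silence. What stands is the case where participation itself is ended: the article states that route, and only questionnaires are explicitly promised after a stop.

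A reader might also infer that lost follow-up undermines the adverse-event tests. Those compare the occurrence of any event and of any grade 3 or higher event. A patient stopped for severe side-effects needing hospitalisation has normally had the qualifying event before she leaves. The objection holds, and it narrows the effect of lost follow-up to three-month BMI, later laboratory values, later events and stops for BMI alone. It does not answer exclusion from the safety set, which would remove the triggering event as well.

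It can be said that the per-protocol-only rule is a defect in its own right, whatever the stopping text says. That is true. The two meet in the same patients, however, and repairing follow-up without the analysis set would leave the added data unused.

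The ethics trigger is narrower than the stopping list, since it covers harm from taking part and not chemotherapy toxicity or unrelated illness. It also protects participants from study-only procedures, and the fix must keep that protection. Finally, routine data are available: "Clinical routine data assessments will be stored in the respective" patient's clinical files. Being retrievable is not the same as being planned for collection and analysis.

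**Conclusion.** The point holds as a cheap improvement that should be made. Followed as written, the rules can end follow-up for patients selected for harm, at the discretion of an unblinded investigator, and may exclude them from the only safety comparison.

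It rests on the natural reading of the back-reference and on two unknowns: how often participation, and not only the diet, would be ended, and whether a stop for harm counts as a major protocol violation. A patient stopped in a later cycle could still qualify for the set requiring one completed cycle.

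Neither size nor direction of a between-arm bias can be computed. A reader might infer that fasting would be made to look safer. The documents do not support that, because the hospitalisation criteria can be met in both arms. The 0.13 BMI points and the 10-point event-rate difference show the mechanism under assumed inputs and should not be quoted as estimates. Most later laboratory values should be retrievable from routine care, and the safety outcomes are secondary and exploratory. The primary fatigue outcome is less exposed, since questionnaires are still requested.

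**What to change.** - **Stopping text and ethics statement:** state that these criteria end the intervention, together with any study-only procedures considered harmful, but not follow-up. The clinical team stays free to stop fasting at once.
- **Follow-up:** continue questionnaires, CTCAE grading, weight and routine laboratory values within the protocol on the Table 1 schedule, identically in both arms, unless the patient withdraws consent to follow-up.
- **Case report form:** record the type of stop (diet only, or consent to follow-up withdrawn), its date and its reason.
- **Statistical analysis:** replace the per-protocol-only safety rule with a safety analysis of all randomised patients who received the first chemotherapy cycle, in their randomised group and including data after a stop. Keep per-protocol safety as supplementary.

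The cost is wording in three sections, one case report form item and a little more data collection after a stop, mostly at visits that are already routine. Two ethics committees approved the current protocol version, so an amendment will probably be needed.
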